**RACF enrolment**								
Eligibility screen	x							
Consent	x							
Allocation		x						
**Intervention**								
KB recruitment		x						
Intervention implementation			x	x	x	x	x	
**Data collection/assessments**								
RACF-level demographic information			x	x	x	x	x	Clinical and administration records; psychotropic register
RACF-level Guideline concordance			x	x	x	x	x	Prescribing and administration records, nursing progress notes, medical records, psychotropic register, behaviour support plans
RACF-level prevalence of medication and behavioural incidents			x	x	x	x	x	RACF Serious Incident Response Scheme
RACF-level proportions of hospitalisations, falls and major injury, polypharmacy, QoL, ADL			x	x	x	x	x	National Aged Care Mandatory Quality Indicator Program records
KB demographics			x					Knowledge brokers
KB activities			x	x	x	x	x	Local action plans, discussion board, quarterly interviews

Abbreviations: *ADL* activities of daily living, *KB* knowledge broker, *RACF* residential aged care facility, *QoL* quality of life, *-t* prior to baseline

#### RACF-level demographic information

Aggregated RACF-level demographic data will be collected from each RACF using a standard data collection form and will include the following: resident bed-days per quarter, proportion of residents who are female, median/mean resident age, proportion of residents with documented diagnosis of cognitive impairment or dementia and proportion of residents using psychotropic medications (antipsychotics, antidepressants, benzodiazepines, z-drugs, opioids and anticonvulsants).

#### RACF Guideline concordance

Trained nurses and health or care professionals will assess Guideline concordance using a standard data collection form completed online (preferred) or in a paper-based version. The data collection form will include questions to assess concordance with indicators for each medication context (Tables 5, 6 and 7). This will require trained nurses and health or care professionals at each participating aged care provider organisation to assign each resident a unique trial identification number. Each aged care provider organisation will securely store the spreadsheet of each resident’s trial identification number, and this will only be accessed by appropriate staff employed by the aged care provider organisation, as needed for care delivery. The Project Management Team will not have access to this information and will not be able to identify residents.

**Table 5 Tab5:** Indicators to assess aggregate RACF-level concordance: antipsychotics

	***Indicators to assess aggregate RACF-level concordance***	***Corresponding Guideline recommendations***
1	Residents using antipsychotics have documentation of experiencing distressing psychotic symptoms and/or aggression/agitation within the past 12 weeks that represents a direct threat to either the resident or other residents, staff, or family for the resident’s prescription of the antipsychotic	GPS 9; CR 3
2	Residents using antipsychotics have documentation of individually targeted non-pharmacological management strategies to manage distressing psychotic symptoms and/or aggression/agitation that are currently in place	GPS 6
3	Residents using antipsychotics are using a second-generation antipsychotic	CR 1
4	Residents using antipsychotics have documentation of informed consent for use of the antipsychotic	GPS 8
5	Residents using antipsychotics have a documented date of next review for antipsychotic treatment effectiveness	GPS 10
6	Residents using antipsychotics have a current antipsychotic adverse event monitoring protocol in place	GPS 20
7	Residents using antipsychotics have used the current antipsychotic for less than 12 weeks	GPS 19; GPS 21
8	Residents using antipsychotics for more than 12 weeks are currently having the antipsychotic dose tapered	GPS 19; GPS 23
9	Residents using antipsychotics for more than 12 weeks and not currently tapering have documentation that the resident has been reviewed by either a psychiatrist or geriatrician, a formal documented discussion between the prescriber and a psychiatrist or geriatrician in which both practitioners agree or a documented clinical review involving the prescriber and at least one other medical practitioner in which both practitioners agree	GPS 19; GPS 21; GPS 22

Abbreviations: *RACF*, residential aged care facility; *GPS*, good practice statement; *CR*, conditional recommendation. GPS and CR refer to those in the Clinical Practice Guidelines for the Appropriate Use of Psychotropic Medications in People Living with Dementia and in Residential Aged Care

**Table 6 Tab6:** Indicators to assess aggregate RACF-level concordance: benzodiazepines for sleep disturbance

	***Indicators to assess aggregate RACF-level concordance***	***Corresponding Guideline recommendations***
1	Residents using benzodiazepines have documentation of individually targeted non-pharmacological management strategies for sleep disturbance that were trialled for an adequate period of time prior to commencing the benzodiazepine	GPS 26
2	Residents using benzodiazepines have documentation of individually targeted non-pharmacological management strategies to manage sleep disturbance that are currently in place	GPS 6
3	Residents using benzodiazepines have documentation of informed consent for use of the benzodiazepine	GPS 8
4	Residents using benzodiazepines have a documented date of next review for benzodiazepine treatment effectiveness	GPS 10
5	Residents using benzodiazepines have a current benzodiazepine adverse event monitoring protocol in place	GPS 28
6	Residents using benzodiazepines have used the current benzodiazepine for less than 2 weeks	GPS 26
7	Residents using benzodiazepines for more than 2 weeks are currently having the benzodiazepine dose tapered	GPS 29
8	Residents using benzodiazepines for more than 2 weeks and not currently tapering have documentation of a review of the harms and benefits of benzodiazepine continuation	CR 6

*Abbreviations*: *RACF*, residential aged care facility; *GPS*, good practice statement; *CR*, conditional recommendation. GPS and CR refer to those in the Clinical Practice Guidelines for the Appropriate Use of Psychotropic Medications in People Living with Dementia and in Residential Aged Care

**Table 7 Tab7:** Indicators to assess aggregate RACF-level concordance: antidepressants

	***Indicators to assess aggregate RACF-level concordance***	***Corresponding Guideline recommendations***
1	Residents using antidepressants have documentation of moderate or severe major depressive disorder	CR 9
2	Residents using antidepressants have documentation of individually targeted non-pharmacological management strategies that are currently in place	GPS 6
3	Residents using antidepressants have documentation of informed consent for use of the antidepressant	GPS 8
4	Residents using antidepressants have a documented date of next review for antidepressant treatment effectiveness	GPS 10
5	Residents using antidepressants have a current antidepressant adverse event monitoring protocol in place	GPS 36
6	Residents using antidepressants have used the current antidepressant for less than 6 months	CR 11
7	Residents using antidepressants for more than 6 months are currently having the antidepressant dose tapered	GPS 37
8	Residents using antidepressants for more than 6 months and not currently tapering have documentation of a review of the harms and benefits of antidepressants continuation	CR 11

*Abbreviations*: *RACF*, residential aged care facility; *GPS*, good practice statement; *CR*, conditional recommendation. GPS and CR refer to those in the Clinical Practice Guidelines for the Appropriate Use of Psychotropic Medications in People Living with Dementia and in Residential Aged Care

Non-identifiable data will be aggregated by Monash University and transferred to Aspect Health using a secure transfer system for the purpose of computing RACF-level Guideline concordance. These data will be fed-back to participating RACFs on a quarterly basis using an electronic dashboard system developed by Aspect Health. Aspect Health is a Queensland-based medication management provider. Aggregated non-identifiable data will be treated confidentially and stored on Aspect Health’s secure server. Each RACF will be able to view their Guideline concordance, compared against the Guideline concordance across their organisation and compared against national Guideline concordance (i.e. aggregate concordance of all participating RACFs) via a secure, password-protected login process. Aggregated data will be reported as proportions or percentages to avoid any potential for RACF re-identification. Aggregated Guideline concordance will be used by the knowledge broker to evaluate quality improvement initiatives and facilitate benchmarking across RACFs and aged care provider organisations.

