### Outcomes

#### Primary outcome

The primary outcome will be the proportion of residents with Guideline concordant use of antipsychotics, benzodiazepines and antidepressants measured at the RACF-level. This outcome will be measured at the 6-month time point, informed by a similar study conducted in RACFs [42]. This overall Guideline concordance will be measured as a dichotomous outcome (i.e. concordant vs not concordant among those using the reference medication) (Additional file 2). This trial-specific composite outcome has been developed from a series of indicators for each medication contexts and developed by New South Wales Therapeutic Advisory Group.

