#### Secondary outcomes

Secondary outcomes will include:Proportion of residents with Guideline concordant use of antipsychotics, benzodiazepines and antidepressants measured at the RACF-level at 3-, 9- and 12-month time points. The 9- and 12-month time points will be used to evaluate intervention sustainability and will be useful for assessing policy and practice change that did not occur at the 6-month time point.Proportion of residents concordant with each individual indicator of the Guideline concordance composite outcome for antipsychotics, benzodiazepines and antidepressants use, measured at the RACF level at 3-, 6-, 9- and 12-month time points (Tables 5, 6 and 7).Proportion of residents using psychotropic medications (antipsychotics, antidepressants, benzodiazepines, z-drugs, opioids and anticonvulsants) measured at the RACF level at 3-, 6-, 9- and 12-month time pointsProportion of residents with hospitalisation, falls, falls with major injury, polypharmacy, quality of life and activities of daily living measured at the RACF level at 3-, 6-, 9- and 12-month time pointsProportion of residents with medication incidents and behavioural incidents measured at the RACF level at 3-, 6-, 9- and 12-month time pointsThese proportions will be calculated using the total number of residents at each RACF at each of the time points as a denominator.

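### The individual-indicator secondary outcomes score three mutually exclusive duration branches separately and over all residents, so their results can mislead

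*Protocol article*

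**What the plan says.** The section RACF Guideline concordance lists nine indicators for antipsychotics (Table 5) and eight each for benzodiazepines and antidepressants (Tables 6 and 7). The last three in each table divide users by duration of use. For antipsychotics they are:

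- indicator 7, short use: "Residents using antipsychotics have used the current antipsychotic for less than 12 weeks"
- indicator 8, tapering: "Residents using antipsychotics for more than 12 weeks are currently having the antipsychotic dose tapered"
- indicator 9, reviewed: "Residents using antipsychotics for more than 12 weeks and not currently tapering have documentation that the resident has been reviewed" (the text goes on to define the review)

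Indicators 6 to 8 of Tables 6 and 7 have the same structure. Their short-use items read "Residents using benzodiazepines have used the current benzodiazepine for less than 2 weeks" and "Residents using antidepressants have used the current antidepressant for less than 6 months".

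The Secondary outcomes section then lists as an outcome, at 3, 6, 9 and 12 months, the "Proportion of residents concordant with each individual indicator of the Guideline concordance composite outcome for antipsychotics, benzodiazepines and antidepressants use". It exempts no indicator and does not say that any are read together. The section closes by setting the denominator for these proportions as all residents in the facility at each time point.

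The Primary outcome section defines the composite differently, as "concordant vs not concordant among those using the reference medication", and refers to Additional file 2 for it. The Sample size and power section also expresses its effect sizes among people taking the medication category.

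**The concern.** The three indicators are branches of one rule, and a resident can meet at most one. When each is scored alone, someone managed along one branch lowers the other two. The short-use item then measures how many residents were recently started or switched, and the tapering item measures how many are part-way through withdrawal. Neither has a clear good direction. More starts raise the first, and successful withdrawal lowers the second.

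The article opens by noting that guidelines advise against routine psychotropic use. A strategy that prevents starts or completes tapers could therefore look worse on items labelled as concordance. The all-resident denominator adds to this, because the indicators are worded for users only. The indicators also feed into the intervention: the Level 3 and Knowledge broker activities sections say that action plans and their goals draw on them.

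**Working it through.** The article gives no figure on this point to reproduce. The check applies the indicator definitions directly.

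**Inputs.** The Background gives 22% regular antipsychotic use. I assume a facility of 100 residents, hence 22 users. The split of those users is also assumed: 4 short use, 3 tapering, 5 reviewed and 10 on none of the branches.

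**Simplest case.** Suppose instead that all 22 users are long-term. Five new starts move the short-use indicator from 0/100 = 0% to 5/100 = 5% of residents, and from 0/22 = 0% to 5/27 = 18.5% of users. Prevalence rises from 22% to 27%.

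**Fuller case.** Each branch cell shows % of residents / % of users. The merged item is (short use + tapering + reviewed) ÷ users.

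| Scenario | Users | Short use | Tapering | Reviewed | Merged item |
|---|---|---|---|---|---|
| Base (4, 3, 5, 10) | 22 | 4 / 18.2 | 3 / 13.6 | 5 / 22.7 | 12/22 = 54.5% |
| Five new starts | 27 | 9 / 33.3 | 3 / 11.1 | 5 / 18.5 | 17/27 = 63.0% |
| Five long-term users on no branch switch drug within the class | 22 | 9 / 40.9 | 3 / 13.6 | 5 / 22.7 | 17/22 = 77.3% |
| Three tapers completed | 19 | 4 / 21.1 | 0 / 0 | 5 / 26.3 | 9/19 = 47.4% |
| Five long-term users on no branch stop | 17 | 4 / 23.5 | 3 / 17.6 | 5 / 29.4 | 12/17 = 70.6% |
| All users reviewed (0, 0, 22, 0) | 22 | 0 / 0 | 0 / 0 | 22 / 100 | 22/22 = 100% |
| Every user on some branch (4, 8, 10, 0) | 22 | 4 / 18.2 | 8 / 36.4 | 10 / 45.5 | 22/22 = 100% |

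The switch row follows from the short-use item counting time on the current drug.

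**What the table shows.**

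1. In the last two rows every user meets a branch, yet the facilities differ on all three separate items (0, 0, 22% against 4, 8, 10% of residents). Only the merged item shows them as equal.
2. The short-use item rises with starts and with switches under either denominator.
3. The tapering item falls to zero when the tapers succeed.
4. The reviewed item does not rise with starts. It is unchanged over residents and falls over users.

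**Generality.** With s short users, l long users and k new starters, the share among users goes from s/(s+l) to (s+k)/(s+l+k). Cross-multiplying, (s+k)(s+l) − s(s+l+k) = kl, which is positive whenever there is at least one long user and one starter. A grid of 3,915 combinations (s from 0 to 14, l from 1 to 29, k from 1 to 9) found no exception under either denominator.

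**The case against.** The strongest reply has five parts.

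**No direction is declared.** The article sets no direction of improvement for single indicators and ranks no facilities. The Effectiveness analysis section commits to a comparison of strategies only for the 6-month primary outcome. Reporting the components of a composite is ordinary practice. This stands: a reader might infer that the plan counts new starts as improvement, but it does not say so. The difficulty is that a proportion called concordant invites that reading.

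**Indicators 8 and 9 carry their own restrictions.** As worded, a short user falls outside the tapering item and does not fail it. This is a fair reading of the tables, but the all-resident denominator overrides it. The reading also leaves two faults. The short-use item has no such restriction, so tapering and reviewed residents still count against it. Among long-term users the tapering item still goes from 3/18 = 16.7% to 0/15 when tapers are completed.

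**Stopping long-term use does raise short use among users.** It moves from 4/22 = 18.2% to 4/17 = 23.5%. This is correct. Only under the stated all-resident denominator does stopping leave the item unchanged, at 4%.

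**Prevalence is reported anyway.** Use of each class is a secondary outcome at the same time points, so extra starts would be seen. This stands as mitigation, but it does not correct the individual items.

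**A merged item is not immune.** It rises with starts (54.5% to 63.0%) and with switches (to 77.3%), and falls with completed tapers (to 47.4%). This is correct, so the merged item must not be read alone.

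**Conclusion.** The point holds for the individual-indicator secondary outcomes. Three exclusive branches per class are scored as separate concordance outcomes, over a denominator that does not match the user-based wording of the tables, the Primary outcome section or the power statement. The gain from new starts is confined to the short-use item: 0% to 5% of residents (0% to 18.5% of users) in the simplest case, and 4% to 9% (18.2% to 33.3%) in the fuller one. The tapering item falls when tapers are completed. The reviewed item misleads only in that residents on another branch count against it.

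The facility counts are assumptions. The direction of the start effect is not, provided there is at least one long-term user.

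Two stronger readings are not supported. A reader might infer that all three branch items reward starting treatment, but only short use does. A reader might also infer that the primary composite requires indicators no resident can meet together. Its combination rule is in Additional file 2, which is not shown and may already treat the branches as alternatives. The primary outcome and the power statement are therefore not in question here, and the point takes no position on the duration limits.

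**What to change.** In the Secondary outcomes section:

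1. Use users of the medication class as the denominator for the concordance indicators, in line with the Primary outcome and Sample size sections. Keep all residents as denominator for prevalence and the other outcomes.
2. Replace the three branch items in each class with one *duration pathway met* indicator: short use, or tapering, or documented review, each as the tables already word it.
3. Report the three branches descriptively, as a split of users with no direction of improvement.
4. Read the merged item beside the class prevalence already collected and, where they can be derived, counts of starts and cessations. This is needed because the merged item still moves with starts, switches and completed tapers.

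The cost is a change of wording in one section. No new data are required, and the primary outcome and clinical thresholds stay as they are. What is lost is the three branches as separate pre-specified outcomes, though their figures would still be reported.

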#### RACF-level prevalence of psychotropic medication use

RACF-level prevalence of psychotropic medications (including antipsychotics, benzodiazepines, antidepressants, z-drugs, opioids and anticonvulsants) will be calculated by number of residents administered psychotropic medications in the last 7 days (regular and pro re nata (PRN)) divided by total number of residents assessed at the RACF. These data will be extracted from audit reports of the medication records of each RACF.

#### RACF-level proportions of hospitalisation, falls, falls with major injury, polypharmacy, quality of life and activities of daily living

Data on RACF-level proportions of hospitalisation, falls, falls with major injury, polypharmacy, quality of life and activities of daily living will be extracted from the mandatory National Aged Care Quality Indicator Program records into a standard data collection form [37]. The following definitions will be used in line with the National Aged Care Quality Indicator Program:Hospitalisation: RACF-level proportion of residents with hospitalisation compared to baseline. Hospitalisation will be assessed as residents who had one or more emergency department presentations or hospital admissions within the last 3 months.Falls: RACF-level proportion of residents falls compared to baseline. A fall event (one or more) will be assessed as an event that results in a person coming to rest inadvertently on the ground or other lower level within the last 3 months [37].Falls with major injury: RACF-level proportion of residents falls with major injury compared to baseline. Falls with major injury will be assessed as a fall event (one or more) that resulted in a major injury or injuries within the last 3 months.Polypharmacy: RACF-level proportion of residents’ polypharmacy compared to baseline. Polypharmacy will be assessed as residents who were prescribed nine or more medications at the time of data collection. Topical preparations, dietary supplements, short-term medications (e.g. short-course antibiotics) and PRN medications will be excluded.Quality of life: RACF-level proportion of residents who report “good” or “excellent” quality of life as assessed using the Quality of Life Aged Care Consumers (QOL-ACC) tool compared to baseline [38]Activities of daily living: RACF-level proportion of residents who experience a decline in their activities of daily living assessment total score of 1 or more points within the last 3 months. Activities of daily living will be measured using the Barthel Index of Activities of Daily Living [39].

#### RACF-level prevalence of medication and behavioural incidents

Data on RACF-level prevalence of medication incidents and behavioural incidents will be collected from each RACF’s electronic risk management system and Serious Incident Response Scheme (SIRS). As in previous research, medication incidents will be categorised according to the severity and type (e.g. an administration error, adverse drug reaction, resident error, pharmacy dispensing error or prescribing error) [40]. Incidents recorded in SIRS include unreasonable use of force (e.g. hitting, pushing, shoving or rough handling a resident), psychological or emotional abuse and inappropriate use of restrictive practice [41].

#### Knowledge broker demographics

Demographic (age, gender) and professional background (education, qualifications, accreditation status and practice experience) data will be collected from the knowledge brokers at the time of enrolment using a standard data collection form completed online (preferred) or a paper-based version.

#### Knowledge broker activities

Data from local action plans and knowledge broker discussion board posts will be collected throughout the trial period. Data from the local action plans will include the following:Goals for improvement (informed by the Guideline indicators)Type of local activities implementedResources used to develop activitiesTimeline for implementation of activitiesWhether or not the activity was implemented

Quarterly, semi-structured interviews and/or focus groups with knowledge brokers may also be conducted throughout the trial. Data will be de-identified and qualitatively analysed to inform on outcomes relating to local process evaluations and facilitators and barriers to change.

